Emerging pilot data suggest that sexual strangulation may be associated with both short-term and longer-term neurological alterations. Specifically, young adult females who have been strangled at least 4 times during sex in the past month showed higher levels of circulating S100B level [26], which is indicative of astroglial activation, increased cortical thickness in widespread brain regions [27], interhemispheric differences in neural activation patterns [28], and inefficient neural effort during working memory tasks compared to strangulation naïve controls [29]. Furthermore, a single event of being strangled during sex was also associated with acute impairments in ocular convergence, blunted positive effects of sexual activities on mental health [30], and elevations in several inflammatory cytokines and chemokines (e.g., CCL-2, VEGF-A) [31]. However, interpretation of these findings has been constrained by methodological limitations, including reliance on a cross-sectional design, smaller sample sizes, and limited ability to distinguish pre-existing differences from strangulation-related effects.

A critical gap is the absence of longitudinal, multimodal studies capable of characterizing neurological health at baseline, assessing acute responses following sexual strangulation, and tracking cumulative effects over time. Without such data, it remains unclear whether observed neurological differences reflect pre-existing vulnerabilities, transient brain responses, or progressive neural changes associated with repeated exposure. Additionally, little is known about how contextual variables, such as frequency, methods, perceived consent, and subjective experiences, may modify neurological outcomes.

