#### Cumulative effects.

To determine whether cumulative exposure to sexual strangulation is associated with longitudinal changes in neurological health, we will model repeated neurological outcomes collected every 6 months over 30 months using GLMMs (or linear mixed-effects models for continuous outcomes), a similar model structure to the acute aim. Each model will include a participant-specific random intercept to account for within-person correlation. Time will be modeled as a categorical variable (baseline, 6, 12, 18, 24, 30 months) for primary analyses to allow non-linear trajectories, and as a continuous variable in sensitivity analyses.

Primary longitudinal analysis will focus on: (1) overall group differences in trajectories between the strangulation and control groups via group × time interaction, and (2) within-group change over time (especially within the strangulation group) to identify when divergence from baseline emerges. Covariates will include age, prior concussion history, mental health diagnosis, and other clinically relevant time-varying factors assessed at each visit (e.g., mental health symptoms, substance use). For imaging outcomes, motion indices will be included.

To directly test the exposure-response hypotheses, we will incorporate time-varying measures of sexual strangulation exposure (e.g., frequency since last visit and cumulative frequency across follow-up; and, where available, intensity/duration and presence of alteration in consciousness) as predictors of neurological outcomes within the strangulation group. These models will estimate whether higher exposure is associated with worse neurological outcomes and whether this association strengthens over time by including exposure × time terms when appropriate.

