A key strength of the proposed study is its prospective, longitudinal design combined with semi-structured interviews that capture the contextual and experiential dimensions of sexual strangulation. Sexual strangulation occurs across a spectrum of motivations, intensities, and consent dynamics, and these factors may modify neurological risk. By characterizing frequency, methods, perceived consent, AIC, and associated symptoms, this study will help identify behavioral patterns that may amplify or mitigate neurological effects. While the observational design precludes causal inference, the temporal resolution afforded by acute and repeated follow-up assessments strengthens inference regarding exposure-response relationships.

Collectively, this study is designed to move the field beyond cross-sectional observation toward a temporally informed understanding of the neurological correlates of sexual strangulation. By integrating multimodal neurobiological, cognitive, visual, and behavioral data, the findings are expected to inform clinical awareness, guide future mechanistic and interventional research, and provide empirical evidence needed to support sexual health education and harm-reduction strategies. As sexual strangulation is now prevalent among young adults, rigorous scientific evaluation of its potential neurological consequences is essential to inform evidence-based guidance, screening, and prevention efforts.

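### The longitudinal exposure-response coefficient mixes within-woman change with stable differences between women, so unadjusted stable traits can appear as exposure-response

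*Protocol article*

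**What the plan says.** Under Cumulative effects, the protocol fits mixed models to outcomes at baseline and at 6, 12, 18, 24 and 30 months. On the random part it says: "Each model will include a participant-specific random intercept to account for within-person correlation". For exposure-response, "we will incorporate time-varying measures of sexual strangulation exposure (e.g., frequency since last visit and cumulative frequency across follow-up", with intensity, duration and alteration in consciousness where available, "as predictors of neurological outcomes within the strangulation group. These models will estimate whether higher exposure is associated with worse neurological outcomes". Exposure × time terms are added when appropriate.

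On adjustment: "Covariates will include age, prior concussion history, mental health diagnosis, and other clinically relevant time-varying factors assessed at each visit". Mental health symptoms and substance use are given as examples of the time-varying factors. No person-mean term, person-mean centring or fixed-effects model is named for exposure.

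Two other places show what the model is meant to achieve. The Introduction criticises earlier studies for "limited ability to distinguish pre-existing differences from strangulation-related effects". The Discussion says that "the temporal resolution afforded by acute and repeated follow-up assessments strengthens inference regarding exposure-response relationships", and its neuroimaging paragraph presents the repeated time points as a way to tell pre-existing vulnerability from adaptation and progressive change.

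**The concern.** A random intercept allows for correlation between a woman's visits, but it assumes that her personal level is unrelated to her exposure. If the two are related, the exposure slope picks up part of that relation. The coefficient then averages two different quantities: how a woman's outcome moves when her own exposure moves, and how women with higher usual exposure differ from women with lower usual exposure. Stable traits confound the second.

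Several such traits are collected but not named as covariates for this analysis: childhood adversity (Baseline assessment), personality (Psychiatric and mental health questionnaires) and partner context (Semi-structured interviews).

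At stake is the first half of hypothesis 3a, that frequent strangulation correlates with worse outcomes. A significant main effect could reflect, in part, which women are strangled more often, and the stated model gives no way to tell.

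**Working it through.** **The plan's own figure.** The Sample size section claims more than 80% power for longitudinal exposure-response effects (d = 0.50, alpha 0.01, 20% loss or switching). It gives no repeated-measures correlation, so the claim can be neither reproduced nor refuted, and this point does not depend on it.

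**Inputs.** From the protocol: 6 visits, random intercept, categorical time, strangulation group only, and 100 women, of whom 80 remain after 20% loss. Assumed: outcome ICC (ICCy), exposure ICC (ICCx), and the correlation ρ between a woman's usual frequency and her outcome level due to a stable trait. No covariates, and a true within-woman effect of zero.

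**Step 1: weight on the between-woman slope.** For T balanced visits, weight = φB / (W + φB), where
- W = (1 − ICCx)(T − 1)
- B = T·ICCx + (1 − ICCx)
- φ = (1 − ICCy) / (1 + (T − 1)·ICCy)

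With ICCy = 0.7, φ = 0.3/4.5 = 0.0667.
- ICCx = 0.5: W = 2.5, B = 3.5, weight = 0.233/2.733 = 0.085.
- ICCx = 0.7: W = 1.5, B = 4.5, weight = 0.300/1.800 = 0.167.

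Over the wider range ICCx 0.4-0.8 and ICCy 0.5-0.7, the weight runs from 6% to 42%. The estimate leans towards the within-woman slope, but not fully.

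**Step 2: spurious slope.** The between-woman slope is ρ√(ICCx·ICCy) / (ICCx + (1 − ICCx)/T). Multiply it by the weight.
- ICCx = 0.5, ρ = 0.2: 0.118/0.583 = 0.203; × 0.085 = 0.017 outcome SD per exposure SD.
- ICCx = 0.7, ρ = 0.4: 0.280/0.750 = 0.373; × 0.167 = 0.062.

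**Step 3: false rejection at 5%.** The standard error is √[(1 − ICCy) / (n(W + φB))] with n = 80.
- First case: √(0.3/218.7) = 0.037; ratio 0.017/0.037 = 0.47; two-sided rejection about 7.5%.
- Second case: √(0.3/144) = 0.046; ratio 0.062/0.046 = 1.36; rejection about 28%.

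Simulation with the same settings gives 8-29% for the mixed coefficient and 4-7% for the within-woman term.

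**Step 4: wider assumptions, at the 0.01 level of the Sample size section.** Simulation with 80 women, six visits, ICCx 0.4-0.8, ICCy 0.5-0.7 and ρ 0.3-0.5:

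| Exposure measure | Mixed coefficient | Within-woman term |
|---|---|---|
| Frequency | 2.8-65% | 0.4-1.8% |
| Cumulative frequency | 2.8-31% | 0.2-1.2% |

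With ρ = 0 the mixed frequency coefficient rejects in 0.8% of runs, so there is no inflation.

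**Step 5: price of the split.** The standard error grows by the factor √[(W + φB)/W]: √(2.733/2.5) = 1.046 and √(1.8/1.5) = 1.095. Simulation gives 4-9%.

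**Step 6: which within-woman term.** With a truly cumulative effect, the deviation in frequency since last visit detects it in 7-10% of simulated trials, and the deviation in cumulative frequency in 78-87%. A woman strangled often but steadily has almost no deviation in frequency, so her sustained exposure drops out of the first test.

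**The case against.** The best defence is that the parameterisation of a time-varying covariate is detail that an article leaves to the analysis plan, and that centring would not contradict the text. Part of this stands: the protocol never says the exposure is uncentred. But it does fix the random effect, the predictors, the analysis set and the reading of the result. Elsewhere it names within-person contrasts when it wants them, in Acute effects and Switching behavior. The plain reading is a single slope per exposure measure.

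The other objections limit the point:
- The group × time analysis and within-group change remove stable level differences, and the exploratory switcher analysis is a within-person comparison. A reader might infer that the repeated measures are never used against stable confounding; that is not so. The gap concerns the exposure main effects.
- The second half of hypothesis 3a, a strengthening association, is tested by exposure × time. In simulation that term rejects a true null in 4.4-5.1% of runs at nominal 5%, so a stable trait with a constant effect does not distort it.
- Substance use and mental health are adjusted for, so they should not be counted among the uncontrolled traits.
- A reader might infer that the protocol claims repeated visits cure confounding. It does not: the Discussion sentence on stronger inference opens by conceding that the observational design precludes causal inference.
- The split has limits. When a stable trait altered the outcome slope and exposure had no effect, the cumulative-frequency deviation rejected in 85% of simulated trials.

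**Conclusion.** The point holds for the exposure main-effect coefficients. Followed as written, the model mixes within-woman change with stable differences between women, which works against the study's own purpose of separating the two.

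Its size is not fixed by the documents. Under the main assumptions (outcome ICC 0.7, exposure ICC 0.5-0.7, trait correlation 0.2-0.4, 80 women, six visits, no covariates), false rejection is about 8-29% at nominal 5%, against about 4-7% for the within-woman term. Stronger trait correlations or more stable exposure raise it, measured covariates shrink it, and zero trait correlation removes it.

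The documents do not support saying that a significant coefficient would be wholly spurious, or that it would be reported as harm: the protocol speaks of association. Nor is the between-woman difference necessarily all confounding, since it may contain real long-term effects. It should be changed because the remedy is cheap and a choice between slopes made after seeing the data would be open to selection.

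**What to change.** In Cumulative effects:
1. Split each time-varying exposure into the woman's own mean over follow-up and the visit's deviation from that mean. Enter both, and report both with a test that they are equal.
2. Base statements about exposure-related change on the within-woman term of cumulative frequency, and keep the planned exposure × time term.
3. Report the between-woman term as an association open to stable confounding.
4. Do not use the deviation in frequency since last visit as the sole test of hypothesis 3a.
5. State that the split removes stable level confounding only, not time-varying confounding or traits that alter the outcome slope.

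The cost is one extra term per exposure and a standard error about 4-9% larger under the assumptions above, more if frequency hardly varies within women. No new data are needed. Data collection runs to May 2030, so the split can be prespecified before the longitudinal outcomes are analysed.

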#### Switching behavior.

During follow-up, some participants may initiate or discontinue sexual strangulation. We will conduct exploratory analyses among “switchers” using (a) time to initiation/cessation as an “intervention” and (b) within-person pre/post comparisons using mixed models with an indicator for post-switch period. These analyses will be labeled exploratory and interpreted as hypothesis-generating.

#### Semi-structured interview.

Interview data will be coded and analyzed following a thematic analysis approach consisting of five steps following Nowell et al. [43] Our analyses will be guided by the following questions: 1. What styles of strangulation do participants report in terms of neck placement, intensity, and being strangled once vs repetitively in a typical encounter? 2. How does one’s experiences with sexual strangulation change over time in the context of frequency, duration, intensity, and methods that they use? 3. What are the signs and symptoms related to sexual strangulation and to what extent do they change over time? 4. Why do people continue to engage in strangulation or decide to stop? As our earlier interview data were collected from only a single time point, it is critical to understand engagement in sexual strangulation prospectively and to examine change over time. Although these data will be novel and extend the literature on their own, they will also support interpretation of the neurological outcomes. For example, motives of engagement whether it is enjoyable/wanted or simply to please their partner may modulate neurological changes over time.

### Sample size

Sample size estimates were based on power calculations using pilot data and related literature. Pilot data demonstrated moderate to large effect sizes across blood biomarkers (Cohen’s d = 0.52–0.87), resting-state functional connectivity (d ≥ 1.2), and cortical morphology (d = 1.4–2.9). Using a conservative estimate of a moderate effect size (d = 0.60), an alpha level of 0.01 to account for multiple models, and a repeated-measures design, a sample of 60 females per group will provide 80% power to detect within-group acute changes and group-by-time differences. An additional pilot sample of 10 males per group will be included to generate preliminary effect-size estimates. For the cumulative longitudinal analyses, power calculations were informed by pilot data and evidence from related hypoxic and subconcussive injury models demonstrating moderate to large effects. Assuming a conservative effect size of d = 0.50, an alpha level of 0.01, and a worst-case dropout or group-switching rate of 20%, a total of 200 females (n = 100 per group) will provide greater than 80% power to detect group differences and longitudinal exposure-response effects over 30 months. To support hypothesis generation for future studies, an additional pilot cohort of 20 males per group will be included.

## Discussion

Sexual strangulation represents a distinct and understudied form of neurological stress that differs fundamentally from mechanically induced brain injury. Rather than direct impact or acceleration-deceleration forces, strangulation primarily induces transient cerebral hypoperfusion, hypoxia, and subsequent reperfusion, processes known to disrupt neural homeostasis and trigger neuroinflammatory cascades [44,45]. Evidence from preclinical hypoxia-ischemia models and clinical contexts such as non-fatal strangulation and autoerotic asphyxiation indicates that even brief interruptions of cerebral blood flow can elicit axonal stress, astrocyte activation, vascular dysregulation, and blood-brain barrier perturbation [22,46–50]. However, the extent to which these mechanisms operate in the context of consensual sexual strangulation, and whether they manifest as transient, compensatory, or cumulative neurological changes, remains unclear.

Blood-based biomarkers provide a sensitive and temporally dynamic index of neural cellular stress across a range of neurological conditions. Markers such as NF-L, tau, p-tau 181, and p-tau 217 reflect axonal cytoskeletal disruption, whereas GFAP and S100B index astrocytic activation and blood-brain barrier integrity, and UCH-L1 reflects neuronal cell body stress [51–53]. Prior work from our group has demonstrated elevations in subsets of these biomarkers among individuals with recent or frequent exposure to sexual strangulation, as well as acute increases in subset of inflammatory cytokines and chemokines (e.g., CCL2, VEGF-A) following strangulation-involved sexual events [31]. These findings are consistent with the hypothesis that strangulation elicits subtle but detectable axonal and glial responses, potentially driven by hypoxic-ischemic stress and inflammatory signaling. The present study will extend this work by assaying a panel of biomarkers that reflect complementary cellular processes. Thus, this study will help clarify whether sexual strangulation preferentially impacts specific neural pathways (e.g., astrocytic or axonal) or produces broader, system-level neurobiological disruption.

Neuroimaging provides critical insight into the structural and functional correlates of sexual strangulation. Pilot studies from our group have identified alterations in cortical morphology, interhemispheric imbalance in resting-state neural activity, and changes in functional activation during working memory tasks among individuals with frequent sexual strangulation exposure [27–29]. These findings suggest the possibility of compensatory neuroplastic responses to repeated hypoxic stress, particularly in cortical and limbic regions involved in cognition, sensorimotor integration, and mental health regulations. However, cross-sectional designs cannot determine whether such patterns reflect pre-existing vulnerability, adaptive responses, or progressive neural change. By integrating diffusion-based microstructural metrics, resting-state and task-based functional connectivity, and QSM across baseline, acute, and longitudinal time points, the proposed study is uniquely positioned to disentangle these possibilities.

Beyond neurobiological measures, sexual strangulation may influence cognitive, visual, and mental health functioning through mechanisms involving hypoxia, autonomic dysregulation, and psychological stress [7,19,54]. Acute hypoxic events have been shown to disrupt ocular-motor control, retinal integrity, attention, memory, and mood, while repeated exposure may contribute to longer-term symptom burden [55–57]. Our pilot study has demonstrated acute changes in NPC, alterations in mood-related outcomes, and increased reporting of neurological symptoms following strangulation-involved sex. [30] The integration of cognitive testing, ocular-motor and retinal assessments, and validated mental health measures in the present study will allow examination of whether neurobiological alterations are accompanied by clinically meaningful functional changes.

A key strength of the proposed study is its prospective, longitudinal design combined with semi-structured interviews that capture the contextual and experiential dimensions of sexual strangulation. Sexual strangulation occurs across a spectrum of motivations, intensities, and consent dynamics, and these factors may modify neurological risk. By characterizing frequency, methods, perceived consent, AIC, and associated symptoms, this study will help identify behavioral patterns that may amplify or mitigate neurological effects. While the observational design precludes causal inference, the temporal resolution afforded by acute and repeated follow-up assessments strengthens inference regarding exposure-response relationships.

Collectively, this study is designed to move the field beyond cross-sectional observation toward a temporally informed understanding of the neurological correlates of sexual strangulation. By integrating multimodal neurobiological, cognitive, visual, and behavioral data, the findings are expected to inform clinical awareness, guide future mechanistic and interventional research, and provide empirical evidence needed to support sexual health education and harm-reduction strategies. As sexual strangulation is now prevalent among young adults, rigorous scientific evaluation of its potential neurological consequences is essential to inform evidence-based guidance, screening, and prevention efforts.

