## Methods

### Participants

This prospective cohort study will enroll a total of 240 young adults, including 200 females and a pilot cohort of 40 males. Female participants will be assigned to one of two primary groups: individuals with frequent exposure (≥4 times per month) to sexual strangulation (n = 100) and age-matched controls with no lifetime history of being strangled during sex (n = 100). An additional pilot cohort of males (n = 20 per group) will be recruited to generate preliminary data on neurological correlates of sexual strangulation in males. The recruitment is anticipated to start in late February 2026 until March 2029, and all data collection is expected to finish by May 2030. Primary analyses will finish by May 2031. Eligible participants will be between 18 and 26 years of age and recruited primarily from the Indiana University campuses and surrounding community. Longitudinal follow-up of enrolled participants will extend up to 30 months. All participants will provide electronic written informed consent prior to enrollment. The initial study protocol has been approved by the Indiana University Institutional Review Board (#27400) on Jun 04, 2025. Upon completion of primary and secondary analyses, all relevant data will be made publicly available in sites including *brainlife* and inter-university Consortium for Political and Social Research (ICPSR).

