Inclusion and exclusion criteria are summarized in Table 2. For the strangulation group, inclusion requires self-report of being strangled during sex at least four times in the month prior to enrollment, which will be verified during a screening interview. Control participants must report no lifetime history of sexual strangulation. Exclusion criteria are limited to conditions necessary for participant safety or study feasibility and include head or neck injury in the past 6 months including concussions, current diagnosis of psychosis, schizophrenia, and seizure disorder, currently taking anti-psychotic medicine, history of brain aneurysm or brain tumor, and current pregnancy. Common psychiatric conditions prevalent in young adults, including depression, anxiety disorders, bipolar disorder, and attention-deficit/hyperactivity disorder (ADHD), will not be excluded and will be assessed and accounted for analytically. Additionally, participants with implanted metal/electro/magnetic devices will not undergo MRI data collection, but they will complete all other assessments; thus, not excluded from the study.

**Table 2 pone.0344672.t002:** Inclusion and exclusion criteria.

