#### Baseline assessment.

Between enrollment and the baseline laboratory visit, participants will complete a series of online questionnaires assessing demographics, medical and neurological history, sexual behavior history, and Adverse Childhood Experiences (ACES). At the baseline visit, participants will undergo various assessments, including testing day questionnaires to gauge various contextual information (menstrual cycle, exercise), capillary blood sampling to test blood fatty acid components, urinalysis to verify pregnancy status, blood sampling for biomarker analysis, MRI, cognitive testing, oculomotor assessments, retinal imaging, and mental health questionnaires. Baseline assessments are designed to characterize neurological health prior to acute or longitudinal exposure assessment and to allow examination of baseline group differences between participants with frequent sexual strangulation exposure and non-strangulation controls. The baseline visit will end with setting up a MyCap account within Research Electronic Data Capture (REDCap) for participants for acute visit purposes. Participants in both the strangulation group and control group will participate in the acute aim (aim 2), but control participants who are not sexually active will not be participating in the acute aim.

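### The Discussion claims the study can separate pre-existing vulnerability from later change, but the strangulation group has no pre-exposure measurement and the planned models cannot date a stable baseline difference

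*Protocol article*

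**What the plan says.** The Introduction sets the gap: without longitudinal multimodal data, "it remains unclear whether observed neurological differences reflect pre-existing vulnerabilities, transient brain responses, or progressive neural changes associated with repeated exposure". The study is then presented as addressing it. The Discussion returns to the same list, noting that "cross-sectional designs cannot determine whether such patterns reflect pre-existing vulnerability, adaptive responses, or progressive neural change", and concludes that "the proposed study is uniquely positioned to disentangle these possibilities".

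Under Participants, the text for the strangulation group says that "inclusion requires self-report of being strangled during sex at least four times in the month prior to enrollment". (Table 2 gives an average of three times in the past month; under either figure these women are already exposed.) The comparison group is "age-matched controls with no lifetime history of being strangled during sex (n = 100". Of the first laboratory visit, the Baseline assessment section says: "Baseline assessments are designed to characterize neurological health prior to acute or longitudinal exposure assessment".

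Under Longitudinal follow-up, participants who change behavior contribute their earlier data to the primary analyses and their later data to exploratory ones. The Switching behavior section plans two exploratory analyses for people who start or stop: one treats the timing of the switch as an intervention, and the other is a within-person pre/post mixed model. The Discussion also states that an observational design does not permit causal inference.

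**The concern.** The Discussion rightly faults cross-sectional work because a difference seen once, after exposure, cannot be dated. The strangulation group's baseline visit has the same limitation. It precedes the exposure recorded on study, not first exposure.

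A difference that is present at baseline and then stays constant is a plausible result, given the cross-sectional pilot differences. It fits a trait that was there before any strangulation, and it fits equally well an effect completed before enrolment. If the report follows the Discussion's wording, such a result could be presented as having been separated from vulnerability when no planned analysis has done so. The findings are meant to inform clinical awareness and sexual health education, so the distinction matters to readers.

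**Working it through.** The plan gives no figure for this point, so there is none to reproduce. The check has two parts.

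**1. Which planned analysis can see vulnerability?**

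| Analysis | Measurement it starts from | What it can inform |
|---|---|---|
| Baseline group analysis | Strangulation group already exposed | A cross-sectional difference; cannot date it |
| Acute effects (group × time) | Already exposed baseline | Transient change after one event |
| Cumulative effects (group × time; exposure-response within the strangulation group) | Already exposed baseline | Progressive change during follow-up |
| Switching behavior, controls who start | Truly unexposed baseline | Change after starting, within person |
| Switching behavior, participants who stop | Exposed baseline | Change after stopping, within person |

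To see why the first three rows leave the question open, write the baseline difference as V + E, with V present before first exposure and E caused by exposure before enrolment. The baseline model estimates V + E adjusted for covariates. The acute and cumulative interactions estimate what is added after enrolment. If nothing is added, V and E remain unseparated. The exploratory mediation models supply no pre-exposure neurological value, so they do not change this.

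The direct test of V is whether controls who later start already differed, before starting, from controls who never start. The data will exist, but no stated analysis makes this comparison. In the primary analyses, starters' earlier visits count as control data.

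**2. How informative could that test be?**

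Inputs: 100 female controls (Participants); alpha 0.01, and a worst case of 20% for dropout or switching combined (Sample size); pilot effects of d = 0.52–0.87 for biomarkers, at least 1.2 for connectivity and 1.4–2.9 for morphology (Sample size). The number of starters is not given. Assumption: k starters out of 100, with k = 20 using the whole 20% allowance and leaving no room for dropout.

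Detectable d at 80% power, two-sided = (z for alpha + 0.84) × √(1/k + 1/(100 − k)).

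For k = 20, √(1/20 + 1/80) = 0.25:
- alpha 0.05: (1.96 + 0.84) × 0.25 = 0.70 (noncentral t: 0.71)
- alpha 0.01: (2.58 + 0.84) × 0.25 = 0.855, about 0.85 (noncentral t: 0.87)

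For k = 10, √(1/10 + 1/90) = 0.333:
- alpha 0.05: 2.80 × 0.333 = 0.93
- alpha 0.01: 3.42 × 0.333 = 1.14

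Noncentral-t power of starters versus never-starters at two-sided alpha 0.01:

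| Starters (assumed) | d = 0.50 | d = 1.2 |
|---|---|---|
| 20 | 27% | 98% |
| 10 | 14% | 83% |
| 5 | 7% | 50% |

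At d = 0.50, alpha 0.05 and 20 starters, power is 51%. These figures are for an unadjusted two-sample comparison. An adjusted time-to-event model would have a somewhat different power.

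**The case against.** The strongest reply is that the plan does hold pre-exposure data and does use them. Controls who start are enrolled unexposed, and a difference that appears only after the switch would argue against a fixed trait. Reversal after stopping would argue the same way, and acute and exposure-response findings also bear on the question. The article labels switcher results as hypothesis-generating and disclaims causal inference. The disputed sentence is in the Discussion and is not a hypothesis or decision rule. An extra exploratory contrast could also sit in a full protocol or analysis plan that is not shown.

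Much of this stands. A reader might infer that no exposed woman will have a pre-exposure measurement, or that no planned analysis uses one. The documents do not support either reading: the first is false for controls who start, and the second is false because of the within-person pre/post model. A reader might also infer that the report will present a stable baseline difference as a consequence of strangulation; no analysis section says so. Nor would the missing contrast be a finding on its own.

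What does not stand is that these points rescue the claim about vulnerability. The within-person analyses ask what follows a switch. They bear only indirectly on whether women who take up the practice differed beforehand. The causal caveat is general, whereas separating prior vulnerability from later change is the specific inference claimed. No analysis plan can supply a pre-exposure baseline for the strangulation group.

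**Conclusion.** The concern holds in a limited form. The claim to disentangle is reasonable for transient and progressive change. It is not supported for pre-existing vulnerability, because the strangulation group is enrolled already exposed and a stable baseline difference fits both explanations. The one direct source of evidence, controls who start, is not used for that comparison.

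The remedy has limited reach. With 20 starters of 100 (assumed), the detectable d of about 0.85 at the protocol's alpha lies above most of the pilot biomarker range of 0.52–0.87, and even at alpha 0.05 the 0.70 lies inside that range. The comparison would be informative for differences the size of the pilot imaging effects (1.2 and above), provided that starters resemble women who are strangled frequently; the documents do not establish this. With 5 or 10 starters it weakens quickly. The design, the aims and the primary models are not invalidated. What needs correction is a stated property that the design lacks.

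**What to change.** 1. In the Discussion, limit the disentangling claim to acute and progressive change. State that pre-existing vulnerability can be examined only in the exploratory subset of controls who start during follow-up.
2. In the Switching behavior section, add an analysis labelled exploratory that compares baseline primary outcomes between controls who later start and those who do not. One form is time to first strangulation regressed on the baseline outcome or a domain composite, which also handles unequal follow-up. Keep covariates few, because events will be few, and state the expected number of starters.
3. State the reading rule in advance: a group difference that does not widen over follow-up will be attributed neither to exposure nor to vulnerability, and a null starter comparison does not rule out vulnerability.

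The cost is one additional exploratory regression per outcome or composite on data already being collected, with no new visits, and a narrower claim. The main drawback is low power: the comparison can detect only large differences and may be uninformative if few controls start.
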